**Trial registration number:**

NCT03588377.

Strengths and limitations of this studyOur study will directly assess impact of pulse oximetry on family referral acceptance by comparing family acceptance of hospital referral (verbal acceptance with hospital visit) in ‘pulse oximetry and clinical signs’ group with ‘clinical signs alone’ group.The study has applicability because it assesses impact with ‘real-life’ limitations (variability in lady health worker accuracy in identifying severe pneumonia, availability of oxygen and human resource at referral hospital and, availability of private transportation).The study design provides means of minimising the effect of confounding.The study design avoids bias in allocation to exposure groups.Blinding is not possible due to nature of intervention.Some subjects may fail to adhere to protocol and non-adherence may cause an underestimated measure of association.

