**Figure 1 F1:**
[figure not shown]
Trial profile. LHW, Lady Health Worker, PO, Pulse Oximetry.

The primary outcome is hospital referral acceptance in children under 5 with severe pneumonia and to identify demographic and clinical predictors of hospital referral acceptance. The predictors will include distance of child home to referral facility, socioeconomic status of household, parental education, child age, nutritional status, respiratory rate, temperature, hypoxaemia and presence of other illnesses.

Secondary outcomes include duration of oxygen therapy, treatment failure, duration of hospital stay, vital and health status of child at day 7th and 14th.

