### Participant

Any child aged 0–59 months having signs and symptoms of acute respiratory illness (cough, fever, difficulty in breathing) in intervention clusters will undergo assessment of (1) signs and symptoms of severe pneumonia and (2) pulse oximetry during monthly LHW home visits. Presence of severe pneumonia with or without hypoxaemia, or hypoxaemia alone will merit hospital referral (non-facilitated). Any child aged 0–59 months having signs and symptoms of acute respiratory illness (cough, fever, difficulty in breathing) in control clusters will undergo assessment of (1) signs and symptoms of severe pneumonia alone. Presence of severe pneumonia will merit hospital referral (non-facilitated). Exclusion criteria will include lack of consent and, non-availability (lost to follow-up, migration) on days of scheduled follow-up visits (days 7 and 14). Those who accepted referral but did not show up at hospital will be included in final analysis.

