#### Procedure at referral facility

Children who accept hospital referral in both intervention and control clusters and reach hospital premises with LHW referral slip will be assessed by study physician at the referral centre. An SMS notification with brief details of referred child will have been provided to trained study personnel (study physician) in advance at time of referral at both the referral facilities. Children with severe pneumonia and/or hypoxaemia as per LHWs who reach referral hospital premises will be examined and subjected to pulse oximetry again by the study physician at referral facility. If signs and symptoms of severe pneumonia are present, the child will be admitted for further appropriate treatment (oxygen therapy via nasal or nasopharyngeal route and intravenous antibiotics, etc) and if the symptoms are not severe (absence of danger sign), the child will be treated in outpatient care as per the standard of referral facility. All the children admitted at referral facility will undergo 12 hourly monitoring by study personnel and filling of CRF and hospital physician form (HPF) at days 1, 7 and 14. Those children who refused the referral will be visited by study community health workers after 24 hours to confirm referral refusal and to fill CRF.

Preliminary meetings will be held with the executive director health Jamshoro, director general health Sindh, in-charge LHW programme Sindh and in-charge paediatric units LUMHS to ensure their cooperation through study duration. Emergency and paediatric unit staff at the referral facilities along with study personnel (physician/nurse) will be trained on management of severe pneumonia according to the integrated management of neonatal and childhood illnesses (IMNCI) guidelines.^34^ A baseline survey will be conducted at the health facilities to ensure availability of oxygen and necessary intravenous antibiotics. Even though it is ideal to guarantee sustainable oxygen systems at the two chosen referral public sector hospitals, this study does not provide oxygen, and therefore, aims to assess ‘real-life’ situations in public hospitals and their impact on severe pneumonia outcomes with or without hypoxaemia. LHWs will be incentivised on basis of their contribution to the study activities.

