### Data analysis

The primary analysis for each outcome will perform on an ‘intention-to-treat’ basis, that is, all children included in the analysis who were enrolled in the study according to the group to which they were allocated. All analyses will account for the cluster randomised design to ensure correct type I error rates and CIs.^35^ Baseline characteristics will be compared by analysing differences in means and proportions among the study arms. Categorical outcomes will be compared using χ^2^ test and continuous outcomes using Student’s t-test. For analysis of predictors of referral acceptance, generalised linear model will be used with logit link function. The univariate analysis will be conducted to explore the independent effect of each predictor on outcome. The variables significant at a liberal p<0.20 will be included in multivariate model for adjustment. The results will be reported as relative risk with 95% CI. Type 1 error will be set at 5% level. All analysis will be done using STATA V.15.

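### The Participant section excludes enrolled children unavailable on days 7 and 14, which contradicts the intention-to-treat rule and would drop children whose referral outcome is already known

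*Protocol article*

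**What the plan says.** The Participant section gives the exclusion rule: "Exclusion criteria will include lack of consent and, non-availability (lost to follow-up, migration) on days of scheduled follow-up visits (days 7 and 14"). The sentence after it reads: "Those who accepted referral but did not show up at hospital will be included in final analysis". The Data analysis section says that the primary analysis of each outcome is by intention to treat, with "all children included in the analysis who were enrolled in the study according to the group to which they were allocated".

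On the outcome, Study aims and design states: "The primary outcome is hospital referral acceptance in children under 5 with severe pneumonia". The strengths and limitations box describes it as "family acceptance of hospital referral (verbal acceptance with hospital visit"). On when it is recorded, Procedure at referral facility says that children who accept and "reach hospital premises with LHW referral slip will be assessed by study physician at the referral centre", and that those who refused will be "visited by study community health workers after 24 hours to confirm referral refusal". Study aims and design lists "vital and health status of child at day 7th and 14th" among the secondary outcomes.

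**The concern.** Whether a child can be found on days 7 and 14 is known only after enrolment. Used as an exclusion criterion, it filters the analysis set on something that happens after randomisation and, for many children, after the primary outcome has been recorded. The intention-to-treat rule keeps such a child; the exclusion rule removes it. Two analysts, each following one of these sections, would report different primary results.

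The arm comparison is also at stake. Blinding is not possible, and families who accept are followed partly through hospital staff while those who refuse are followed at home. Availability could therefore plausibly depend on the outcome, and on the arm as well.

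**Working it through.** **Step 1: is this an entry criterion or an analysis-set rule?** Loss to follow-up cannot be observed at screening. The sentence that follows the rule concerns inclusion in the final analysis. It keeps verbal acceptors who never arrived, but says nothing of the kind for children missed on days 7 and 14. Nothing limits the exclusion to secondary outcomes. As written, it conflicts with the Data analysis section.

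**Step 2: does the primary outcome need those visits?** Refusal is confirmed at a home visit after 24 hours. Acceptance with a hospital visit is recorded when the child reaches hospital. Neither uses the day 7 or 14 visit.

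**Step 3: what could the exclusion do to the estimate?**

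Inputs from the Sample size section: 10% and 15% acceptance, a planned relative risk of 0.15/0.10 = 1.50. The documents give no retention rates, so those below are assumptions.

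Let p be the true acceptance rate, and rA and rR the proportions of acceptors and refusers retained. Then

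observed rate = p·rA / [p·rA + (1 − p)·rR].

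The observed odds equal the true odds times rA/rR. If rA/rR is the same in both arms, the odds ratio is unchanged and the relative risk nearly so. Distortion needs rA/rR to differ between arms.

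Example, acceptors 80% and refusers 95% retained: 0.15×0.80 / (0.15×0.80 + 0.85×0.95) = 0.1200/0.9275 = 12.9%; 0.10×0.80 / (0.10×0.80 + 0.90×0.95) = 0.0800/0.9350 = 8.6%.

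| Control retained (acceptors/refusers) | Intervention retained | True 10% vs 10%: observed (RR) | True 10% vs 15%: observed (RR) |
|---|---|---|---|
| 90/90 | 90/90 | 10.0 vs 10.0 (1.00) | 10.0 vs 15.0 (1.50) |
| 80/95 | 80/95 | 8.6 vs 8.6 (1.00) | 8.6 vs 12.9 (1.51) |
| 95/80 | 95/80 | 11.7 vs 11.7 (1.00) | 11.7 vs 17.3 (1.49) |
| 90/90 | 80/95 | 10.0 vs 8.6 (0.86) | 10.0 vs 12.9 (1.29) |
| 90/90 | 95/80 | 10.0 vs 11.7 (1.17) | 10.0 vs 17.3 (1.73) |
| 90/90 | 95/70 | 10.0 vs 13.1 (1.31) | 10.0 vs 19.3 (1.93) |

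With equal patterns in both arms (rows 2 and 3), the rates shift but there is no false effect under the null, and the relative risk stays at 1.49 to 1.51. With differing patterns, bias can go either way. In row 5 with no true effect, starting from 2,080 enrolled per arm, about 1,872 control children (2,080×0.90) and 1,695 intervention children (2,080×[0.10×0.95 + 0.90×0.80]) remain. With 22 children per cluster the design effect is 1 + 21×0.001736 = 1.036, and a nominal two-sided 5% test rejects about 35% of the time.

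**Step 4: is lost power the issue?** No. Spreading 4,160 children over 188 clusters gives 22.1 per cluster and a design effect of 1 + 21.1×0.001736 = 1.037. Power for 10% versus 15% is then about 99.8% with no exclusions, 99.5% with 10% excluded and 99.1% with 20% excluded. These inputs do not reproduce the stated 4,160 at 90% power. The cluster size behind that figure is not given, and the question is separate from this one.

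**The case against.** The strongest reply is that the rule may have been meant for families expected at screening to be away, and that the full protocol may say so. The article does not, and loss to follow-up is not a screening finding. The contradiction stands.

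Several stronger readings are tempting but not supported:

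- *The primary outcome is known within a day for every child.* This is explicit only for refusers. No arrival window is given for acceptors, and the article does not say when non-arrival of a verbal acceptor is settled. The Trial setting section also describes the day 7 and 14 visits as being for outcome measurement without restricting which outcomes. What holds is that acceptance, as the article describes its recording, does not rely on those visits.
- *Acceptors will be lost because they are inpatients.* Procedure at referral facility has forms completed for admitted children on days 1, 7 and 14, so inpatients are covered.
- *The primary result will be biased.* Outcome-related loss alone hardly moves the relative risk, which is the measure named in the Data analysis section. The patterns that distort it are assumed, not sourced.
- *The numerator is defined in two conflicting ways.* The Participant section keeps verbal acceptors who did not arrive in the analysis; it does not say they count as acceptances. They can stay in the denominator as non-acceptors, consistent with the strengths and limitations box. The word acceptance is used loosely, which calls only for clarification.
- *The outcome means arrival at the designated referral hospital.* The box says only a hospital visit.

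**Conclusion.** The plan is wrong as written: the day 7/14 exclusion contradicts the intention-to-treat rule and would remove enrolled children with known primary outcomes.

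The size of the bias is conditional. Under a planned relative risk of 1.50, availability that depends on outcome equally in both arms leaves 1.49 to 1.51. Availability that differs by both arm and outcome gives 1.29 to 1.93, and under no true effect 0.86 to 1.31, in the scenarios tried. All of these rest on assumed retention. A reader might infer that the trial's result is compromised; the documents support only that the rule creates an avoidable risk in an unblinded trial. The loss of power is negligible.

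**What to change.** 1. In the Participant section, delete non-availability on days 7 and 14 from the exclusion criteria.
2. State that every consented, enrolled child is analysed for referral acceptance in the allocated group.
3. Treat day 7/14 non-availability as missing data only for the secondary outcomes that need those visits, and report it by arm and by referral outcome.
4. As a wording clarification, state that children whose families accepted verbally but made no hospital visit stay in the denominator and, under the definition in the strengths and limitations box, do not count as accepted.

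The cost is a few sentences in the protocol and analysis plan. No new data or change to the target of 4,160 is needed, and the analysable sample can only grow. The Study status section reports 235 + 184 = 419 children enrolled with recruitment continuing, so there was still time to settle the rule before analysis.

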### Randomisation and masking

Study clusters were defined as the area covered by an LHW. Each LHW covers a minimum of 100 households. A list of LHWs working in Kotri was collected from the LHW programme, health department government of Sindh. There are a total of 188 active LHWs in the study site. A baseline survey was conducted to collect data on health indicators from the LHW catchments. The clusters were randomly allocated to intervention and control groups on 1:1 fashion with a computer-generated randomisation sequence that was generated by an independent expert. Clusters were matched on under 5 population and distance to referral health facility. No stratification was used for allocation; clusters were selected to ensure that the reporting and training centres of intervention and control LHWs were separate. The investigators and the national and provincial LHW programme coordinators will be excluded from the allocation process.

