### Trial setting

The study will be conducted within the community of Taluka Kotri in District Jamshoro, Sindh (figure 2). Jamshoro District has a population of 993 142.^31^ It is predominantly rural, with 33% literacy, and >50% employed daily wage labourers. A baseline survey conducted as a part of current study showed the status of overall health indicators: skilled birth attendance 57%, antenatal care coverage 75%, postnatal care cover for mother and newborn within 48 hours 31.5%, vaccination completeness in children 12–23 months 68% and care seeking for ARI and diarrhoea >80% (internal survey). A total of 27 health facilities function in the district including 1 district headquarter (DHQ) hospital, 3 taluka headquarter hospitals, 5 rural health centres and 18 basic health units. The district is divided administratively in 30 union councils. Kotri is one of the four Talukas of Jamshoro, consists of 44% (437 561) of the population of district.^31^

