### Sample size

Defining a cluster as (the catchment area of) one LHW, and assuming a power of 90% in detecting 50% increase in referral acceptance from a 10% baseline to 15% among children aged 0–59 months with severe pneumonia (pneumonia prevalence at 2-week recall (MICS Sindh): 7.5% (18% of which is assumed severe pneumonia) with ICC 0.001736. We need to capture a total of 4160 children with severe pneumonia in both intervention and control groups.

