### Limitations

Some union councils with poor LHW coverage were not included in this study. This was a compromise on generalisability in favour of feasibility. It may have led to exclusion of children whose referral patterns were important to gauge. We also did not offer facilitated referral in either arm. This may have affected referral acceptance in both groups, however, will allow assessment of real-life impact of transportation barriers.

Though we kept hospital referral (as recommended by WHO) for severe pneumonia as our standard of care, it was beyond the scope of this study to ensure that referral centres had sustainable oxygen systems/capacity for non-invasive ventilation in children with severe pneumonia, or readily available cardiac evaluation resources for children with hypoxaemia alone. Duke *et al* showed improved case fatality rates by providing oxygen concentrators and pulse oximeters at five hospitals in PNG along with protocols for use.^35^ Lack of quality care at referral hospitals in developing countries is a recognised barrier to healthcare seeking behaviour.^40 41^

If our study reveals pulse oximetry has influenced health-seeking behaviour significantly, we will need to follow with a more systematic evaluation of pneumonia care at rural hospitals which vary in quality of care. We will also need to correlate recovery rates in those who accepted hospital referral versus those who stayed home on oral amoxicillin. Evidence to support home care for severe pneumonia is poor.^42^

The COVID-19 pandemic has adversely affected recruitment in the study with disruption of field activities for many months in 2020. We anticipate prolongation of study duration in order to achieve sample size.

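### The primary arm comparison is fixed as a chi-square test without covariates, although children are enrolled after allocation by unblinded workers and the relevant child and household variables are collected

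*Protocol article*

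**What the plan says.** **Outcome and test.** The primary outcome is acceptance of hospital referral (Study aims and design), which is binary. The Data analysis section states: "Categorical outcomes will be compared using" a chi-square test. It adds in general terms that all analyses allow for the cluster design, and that "Type 1 error will be set at 5% level". No covariates are attached to the arm comparison.

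**Covariate model.** A generalised linear model with logit link is assigned to the predictors of acceptance. Variables enter it if they pass p<0.20 one at a time. Study arm is not named as a term. The listed predictors include child age, household socioeconomic status, parental education and distance to the facility.

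**A second analysis.** The abstract says that an analysis of variance will compare baseline referral acceptance in both groups with that at the end of the study. The Data analysis section does not carry this forward.

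**Baseline data.** Randomisation and masking says: "A baseline survey was conducted to collect data on health indicators from the LHW catchments". Trial setting reports from a baseline survey "care seeking for ARI and diarrhoea >80% (internal survey", one overall figure.

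**Design.** Clusters were matched on under-5 population and distance to the referral facility, and chosen so that the LHWs of the two arms have separate reporting and training centres. Blinding is stated to be impossible. LHWs identify, consent and enrol children after allocation. In intervention clusters, hypoxaemia alone also qualifies a child.

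**The concern.** Randomising clusters balances the catchments in expectation. It does not balance the children whom an LHW later chooses to assess, classify and enrol when she knows her arm. If the enrolled families differ by arm in wealth, education or the child's age, and these affect whether a family goes to hospital, an unadjusted comparison attributes part of that difference to the oximeter.

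Allowing for clustering corrects the standard error; it does not move the estimate. Matching on two catchment-level factors leaves socioeconomic status, education, age and care-seeking unmatched, and the stated test does not use even the matching factors. Choosing covariates by p<0.20 does not help, because it is tied to the predictor objective and lets the data decide what is adjusted for.

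The article also leaves two candidate primary analyses, the abstract's and the Data analysis section's. This is more than silence that an analysis plan would fill: the article names a test, and names a different one elsewhere.

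**Working it through.** **1. The plan's own figure.** Inputs from Sample size: "assuming a power of 90% in detecting 50% increase in referral acceptance from a 10% baseline to 15"%, "with ICC 0.001736", and "We need to capture a total of 4160 children with severe pneumonia in both intervention and control groups". Two-sided 5% and 90% power give 918 per arm, 1836 in total. If all 188 active LHWs are clusters (an assumption, since the number randomised is not stated), there are 4160/188 = 22.1 children per cluster. The design effect is 1 + (22.1 − 1) × 0.001736 = 1.037, and 1836 × 1.037 is about 1903. So 4160 is not reproduced; it is about twice this total. That does not affect the present point, and 4160 (2080 per arm) is used below as stated.

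**2. Ceiling on the precision gain.** If covariates explained all between-cluster variance, the design effect would fall from 1.037 to 1. The saving is 1 − 1/1.037, about 3.5%. The case for adjustment therefore rests on bias.

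**3. Illustration of bias.** The document gives no covariate values by arm and no covariate-outcome associations, so every input here except the sample size and the ICC is an assumption. There is no oximetry effect, and control acceptance is 10%. One covariate x is standard normal in control and shifted by s SD in intervention.

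- Model: logit(p) = a + ln(OR)·x, with a set so that mean acceptance in control is 10% (a = −2.262 for OR 1.5; −2.381 for OR 2).
- SE = √{[0.09 + p₁(1 − p₁)] / 2080 × 1.037}
- z = (p₁ − 0.10)/SE; rejection = Φ(−1.96 + z) + Φ(−1.96 − z)

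Worked case, OR 1.5 and s = 0.2: p₁ = 10.74%; SE = 0.0096; z = 0.77; rejection = 0.12.

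| OR per SD | s | p₁ | Spurious ratio | Rejection, ICC 0.001736 | Rejection, ICC 0.05 (assumed) |
|---|---|---|---|---|---|
| 1.5 | 0.1 | 10.37% | 1.04 | 6.7% | 5.8% |
| 1.5 | 0.2 | 10.74% | 1.07 | 12% | 8.5% |
| 1.5 | 0.3 | 11.13% | 1.11 | 21% | 13% |
| 2 | 0.1 | 10.61% | 1.06 | 9.8% | 7.4% |
| 2 | 0.2 | 11.25% | 1.13 | 25% | 15% |
| 2 | 0.3 | 11.93% | 1.19 | 50% | 28% |

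The last column uses design effect 1 + 21.1 × 0.05 = 2.06.

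**4. Second model as a check.** Take a binary confounder at 50% prevalence in control, with risk ratio 1.5 to 3 and an arm imbalance of 5 to 20 percentage points. The spurious difference is 0.2 to 2.0 points, which is 4% to 40% of the 5-point target. The type I error is 0.055 to 0.53.

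**5. How large chance imbalance would be.** The SE of an arm difference in a standardised covariate is √(2/2080 × design effect): about 0.03 SD at a covariate ICC of 0.001736 and 0.07 SD at 0.2 (assumed). A shift of 0.2 to 0.3 SD would therefore need systematic selection.

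**The case against.** The strongest objection is that a cluster-accounted unadjusted comparison is a valid primary analysis of a randomised trial, that the choice of prognostic covariates usually belongs in the analysis plan, and that a journal article need not list them. This stands for chance imbalance, which a correct test already allows for. It does not answer imbalance from enrolment after allocation, and the article does not leave the test open: it names one, and its abstract names another.

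Nor is nothing done about imbalance. Clusters were matched on distance, which the introduction lists among the main reasons for delayed care. But matching on distance and under-5 population does not reach household and child characteristics.

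The magnitudes are also open to attack, and this stands. Nothing in the document supports a shift of 0.2 to 0.3 SD. At 0.1 SD the rejection rate is 7% to 10%, and with a larger ICC the rates fall.

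Three stronger readings are tempting and are not supported:

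- A reader might infer that the "disruption of field activities for many months in 2020" created imbalance between arms. Limitations gives no difference by arm, and Trial setting says that enrolment runs simultaneously in both. A common interruption does not by itself unbalance them.
- A reader might take the survey's care-seeking figure as a ready baseline for referral acceptance. Only an overall value above 80% is given, against an expected acceptance of 10%, and care-seeking on the family's own initiative is a different behaviour. Whether usable values exist by catchment is not stated.
- A reader might take the enrolment of 235 against 184 (Study status; ratio 1.28) as evidence of covariate imbalance. It shows different yields by arm, to which the wider intervention eligibility could contribute, and nothing about who was enrolled.

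**Conclusion.** The point holds in a limited form. The Data analysis section fixes an arm comparison without covariates for the primary outcome, keeps the collected child and household variables for a predictor model screened at p<0.20, leaves out the matching factors, and disagrees with the abstract. With unblinded enrolment after allocation, measured characteristics can differ by arm, and the stated test would not correct for it. The document does not show that they do differ.

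The size of any bias cannot be derived from the document. Under the stated assumptions, false rejection runs from about 7% to 50% at the plan's ICC; the upper end needs both a strong covariate and a systematic shift of 0.3 SD. The precision gain at that ICC is at most about 3.5%.

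Adjustment would remove only imbalance that is measured and correctly modelled. It would not remove unmeasured selection by the LHW, and it would not repair the wider eligibility in the intervention arm, which makes the two enrolled populations different by definition. A reader should not expect the change below to settle that separate problem.

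**What to change.** In the Data analysis section, name one primary model for referral acceptance that allows for clustering and contains:

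- study arm;
- the two matching factors, under-5 population and distance to the referral facility;
- child age, household socioeconomic status and parental education as fixed covariates, none chosen by p-value;
- baseline ARI care-seeking by catchment, only if the survey gives usable values at that level.

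Report the standardised risk ratio and risk difference, with the cluster-adjusted result without covariates beside them. State that variables which the oximeter reading can influence are not adjusted for. Keep the predictor analysis as a separate objective. Bring the abstract's ANOVA into line with this model, or state what role it has.

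The cost is wording in the protocol and analysis plan. The child and household variables are already on the list of predictors to be collected. The catchment covariate needs a check that the survey can be linked by LHW catchment and is precise enough; if not, leave it out. Study status reports 235 + 184 = 419 of 4160 children enrolled by 16 October 2020, about 10%, so at that date the change could still be made well before the final analysis.

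### Clusters were matched on distance and under-5 population, but the named arm comparison carries neither factor and the p<0.20 screen does not exempt them

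*Protocol article*

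**What the plan says.** Under Randomisation and masking, the protocol article defines a cluster as the area of one LHW and reports 188 active LHWs in the study site. It then says: "The clusters were randomly allocated to intervention and control groups on 1:1 fashion". It adds: "Clusters were matched on under 5 population and distance to referral health facility". The next sentence reads: "No stratification was used for allocation; clusters were selected to ensure that the reporting and training centres of intervention and control LHWs were separate". The section does not say whether matching formed pairs or only balanced two groups, or whether randomisation took place within pairs.

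Under Data analysis, all analyses are to account for the cluster randomised design. The outcome comparison is then named: "Categorical outcomes will be compared using χ^2^ test and continuous outcomes using Student’s t-test". No matching term and no matching factor is mentioned. The abstract refers to analysis of variance, again without the matching.

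The one adjustment rule follows the sentence introducing the logit model for predictors of referral acceptance: "The variables significant at a liberal p<0.20 will be included in multivariate model for adjustment". Distance from the child's home to the referral facility is one of the candidate predictors listed under the study aims. Cluster under-5 population is not listed.

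**The concern.** Factors that shape the allocation normally belong in the analysis. Distance is the more important of the two here. The Introduction names it among the main reasons for delayed care, and the trial treats it as a likely predictor of its own primary outcome.

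Two things are at stake. First, if allocation was constrained by the matching, an analysis without it leaves between-cluster variation in the standard error that the design had removed, so the interval is wider than necessary and some power is lost. Second, the matching shared control of the allocation with another constraint, the separation of reporting and training centres by arm. That constraint is likely to be geographic and can work against balance in distance. The stated arm comparison has no term to correct any imbalance that remains.

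A significance screen is also a poor way to handle a design variable, because whether it enters the model then depends on a chance p-value.

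**Working it through.** **Inputs.** From Sample size: 10% against 15% acceptance, 90% power, ICC 0.001736, total 4160 children. From Data analysis: type I error 5% (two-sided assumed). From Randomisation and masking: 188 LHWs, 1:1. Use of all 188 as clusters is an assumption; it gives m = 4160/188 = 22.1 children per cluster and, if paired, 94 pairs.

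**The plan's own figure.** The documents give no figure for the effect of matching; the nearest one is the sample size.
- Individually randomised: n per arm = [1.960·√(2·0.125·0.875) + 1.282·√(0.10·0.90 + 0.15·0.85)]² / 0.05² = 918, total 1836.
- Design effect: 1 + (22.1 − 1)·0.001736 = 1.037, so the total is about 1903, not 4160.
- One-sided tests, continuity correction, 80% power, 10 to 188 clusters and a coefficient-of-variation formula (k from 0.10 to 0.30) did not come within 3% of 4160 either.
- Reaching 4160 needs a design effect of 4160/1836 = 2.27. At 22.1 children per cluster that is an ICC of (2.27 − 1)/21.1, or about 0.06.

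The mismatch is a separate matter. It is used here only to choose a second ICC at which to size the effect.

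**Effect of leaving out the matching.** Let r be the within-pair correlation of true cluster effects (assumed). The between-cluster share of the variance of a cluster proportion is s = m·ICC / [1 + (m − 1)·ICC]. An analysis that accounts for clusters but not pairs then overstates the standard error by the factor 1/√(1 − r·s).

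- ICC 0.001736: s = 22.1·0.001736/1.037 = 0.037. With r = 1, the factor is 1/√(1 − 0.037) = 1.019, the upper limit at this ICC.
- ICC 0.06: s = 22.1·0.06/2.268 = 0.585. With r = 0.25 the factor is 1/√(1 − 0.146) = 1.08; with r = 0.75 it is 1/√(1 − 0.439) = 1.34.

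| ICC | r = 0.25 | r = 0.50 | r = 0.75 |
|---|---|---|---|
| 0.001736 (stated) | 0.5% | 0.9% | 1.4% |
| 0.02 (assumed) | 4% | 9% | 14% |
| 0.05 (assumed) | 7% | 17% | 29% |
| 0.06 (assumed) | 8% | 19% | 34% |

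Entries are the excess in the standard error.

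**Simulation check.** 94 pairs, 22 children per cluster, r = 0.5; type I error at 10% acceptance in both arms.

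| ICC | unpaired cluster t | paired cluster t | χ² ignoring clusters |
|---|---|---|---|
| 0.001736 | 0.049 | 0.052 | 0.053 |
| 0.02 | 0.034 | 0.050 | 0.072 |
| 0.05 | 0.025 | 0.050 | 0.102 |

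Power at 10% against 15% was 99.8% unpaired and 99.9% paired at the stated ICC, and 95.8% against 97.5% at ICC 0.05.

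**Residual imbalance in distance.** The unadjusted shift is (acceptance near − acceptance far) × (difference between arms in the share living near). The documents give neither quantity. As an illustration only: with 12% near and 8% far, an imbalance of 5, 10 or 20 percentage points shifts the effect by 0.2, 0.4 or 0.8 points, against a planned effect of 5 points.

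**The case against.** The strongest reply is that the article promises to account for the cluster design and is a condensed text. Whether that means pair terms, covariates or cluster summaries can be left to an analysis plan that is not shown. This stands in part: the absence of a pair term is not by itself an error, and nothing says the matching will be ignored. But the article does name tests without the matching factors and fixes a selection rule without an exemption. Those are stated choices that fit poorly with a matched design.

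Four stronger readings are tempting, and the documents do not support them.

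- *A reader might infer that the p<0.20 screen can drop distance from the arm comparison.* The screen is written for the predictor model, and no screened model is stated for the arm comparison.
- *A reader might infer that nothing protects against imbalance in distance.* Matching on distance with 1:1 allocation is protection by design, and the documents show no imbalance. What is missing is adjustment for whatever remains.
- *A reader might infer that the intervals are invalid.* If clustering is handled as promised, the error is conservative. Inflated type I error would come from a χ² test that ignores clusters, which is a different fault.
- *A reader might infer that there are 94 randomised pairs.* The text never says so, and it denies stratification. If matching only balanced the groups, there are no pairs to model and the pair calculations above do not apply.

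It is also fair to say that no passage links cluster under-5 population to acceptance. The case for including it rests only on its role in the design.

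**Conclusion.** The point holds in a limited form. The design is described as matched on two factors, the named arm comparison includes neither, and the only adjustment rule does not exempt them.

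At the protocol's own ICC the loss of precision is minor, at most about 2% of the standard error, and would not change a conclusion at the planned size. It becomes material, at about 8% to 34%, only if the ICC is near 0.06 and pairs are correlated at 0.25 to 0.75. Both are assumptions, as are the use of all 188 clusters and randomisation within pairs. The direction is conservative provided clustering is accounted for.

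The second consequence, unadjusted residual imbalance in distance, cannot be sized from the documents. It is possible because of the separate-centres constraint, but it is not shown. The change is worth making because it costs almost nothing, not because the stated analysis would mislead.

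**What to change.** **Data analysis.** State that the arm effect on referral acceptance comes from a cluster-adjusted model that always includes distance to the referral facility and cluster under-5 population. Limit the p<0.20 screen to the other candidate predictors in the second primary objective. Say which distance is meant: the matching was done on clusters, whereas the listed predictor is measured from the child's home.

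**Randomisation and masking.** State how matching constrained the allocation (pairs or group balance, and whether randomisation was within pairs), and reconcile this with the statement that no stratification was used.

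**If randomisation was within pairs.** Use a paired cluster-level analysis or a pair random effect, not 93 fixed pair terms. At full size a pair would hold about 4160/94 = 44 children and, at 10% acceptance, 4 to 5 acceptances. At the 419 children enrolled by October 2020 (235 + 184) it would hold about 4.5 children, and some 0.9^4.5 = 62% of pairs would have no acceptance at all.

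**Cost.** Wording only. Both factors were already used for the matching, so no new data are needed, and two fixed covariates take few degrees of freedom.
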